#### Additional analyses

2.5.3

Additional statistical tests will be run to aid in interpreting the results and obtain a more nuanced understanding of the findings. Independent *t*-tests and χ^2^-tests will be used to estimate possible between-group pre-treatment differences regarding healthcare service utilization, demographic variables, and eating disorder symptom severity. In case of significant group differences, these variables will be utilized as moderators of the treatment × time interaction effects to test the robustness of the findings. We will further test whether other covariates such as patient outcome expectancies, attitudes towards online interventions, or patient adherence affect changes in the primary outcome. To obtain a higher ecological validity and temporal resolution when examining reductions in core eating disorder symptoms, we will analyze the EMA data and the weekly assessments of binge eating episodes. As patient safety indicators, the percentage of participants in the intervention group who experienced adverse intervention effects caused by the web-based intervention will be quantified, and the amount of impairment due to these negative effects will be calculated. Moreover, we will test potential improvements in emotion regulation difficulties and strategy use as possible mediators of BED symptom change.

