#### Randomization and blinding

2.3.1

After completing the diagnostic interview and the baseline assessment, randomization will be performed in a 1:1 ratio by an independent researcher who is not involved in the project using a computer-based algorithm provided by the software *SoSci Survey* (Leiner, 2021). The diagnostic interviews will thus be conducted blindly; that is, the clinical interviewers do not know what treatment a participant will be allocated to in case of inclusion (*allocation sequence concealment*; Altman and Schulz, 2001). During the clinical interviews, participants are told that the assigned waiting time varies randomly between 0 and 12 weeks to prevent frustration, dropout, or other biases in the control group. Following randomization, all participants receive an email with either a code to immediately access the intervention or information that they will receive a code in 12 weeks. Finally, the group allocation variable will be blinded to allow unbiased data analyses. For this purpose, an independent researcher will delete all information in the data set indicating the group membership.

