#### Primary and secondary outcome analyses

2.5.1

To statistically evaluate the effectiveness of the web-based intervention for patients with BED compared to the waitlist control condition, growth models within a multilevel modeling (MLM) framework will be conducted. MLMs are regression-based models that allow considering the nested data structure, i.e., the three repeated assessments (level 1) nested within patients (level 2), define change as a continuous process, and have more power when handling missing data than traditional approaches (Hesser, 2015; Kahn and Schneider, 2013; Tasca and Gallop, 2009). To test whether there is a treatment × time interaction effect, we will set up MLMs of increasing complexity (Kahn and Schneider, 2013). The first model will have only random intercepts on the person-level (level 1), and no predictors will be included. In the second model, the fixed effects of time (study entrance, 6 weeks, 12 weeks) and treatment (intervention versus control group) will be added. In a final model, we will examine if the change in symptom severity differs between the intervention and control group by adding the treatment × time interaction. Model fit of the competing models will be compared employing likelihood ratio tests for nested models and the Akaike Information Criterion. A significant treatment × time-interaction with a more substantial change in participants undergoing the 12 weeks of treatment compared to the waitlist group will indicate confirmation of the hypotheses (Raudenbush and Bryk, 2002). The magnitude of treatment effects will be estimated as Cohen's *d* effect size (Feingold, 2013).

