### Statistical power and sample size

2.6

To determine the required sample size, we conducted power calculations using the R package *powerlmm* (Magnusson, 2018). Based on previous meta-analytic evidence for the effectiveness of web-based interventions for BED (Beintner et al., 2014; Haderlein, 2022; Hilbert et al., 2019), we chose medium effect sizes of Cohen's *d* = 0.50 as a benchmark for expected pre-post differences between the intervention group and the waitlist control group. Power calculations using an intraclass correlation of .40 (Arend and Schäfer, 2019), a power of .80, and an alpha level of .05 resulted in a required sample of *N* = 152. Additional power analyses, including possible dropouts of 20% and different intra-class correlation coefficients, can be found in the supplementary material (Fig. S3), strengthening our conclusion that our sample will be sufficiently large to detect a medium effect under different statistical assumptions.

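### The robustness model takes its variables from baseline significance tests and enters them as moderators, so chance selects the check and it answers a different question

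*Protocol article*

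**What the plan says.** Section 2.5.1 (Primary and secondary outcome analyses) fixes the effectiveness model as a growth model on "the three repeated assessments (level 1) nested within patients (level 2"), with fixed effects of time, treatment and their interaction. No baseline covariate is named, and confirmation of the hypotheses is tied to that interaction.

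Section 2.5.3 (Additional analyses) then adds a conditional step. Independent t-tests and χ²-tests "will be used to estimate possible between-group pre-treatment differences regarding healthcare service utilization, demographic variables, and eating disorder symptom severity". The consequence of a significant result is fixed: "In case of significant group differences, these variables will be utilized as moderators of the treatment × time interaction effects". The sentence goes on to give robustness of the findings as the aim.

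The section does not list the individual variables within the three families. It does not say whether moderators are centred or which coefficient is to be read as the robustness result. Section 2.3.1 (Randomization and blinding) states that "randomization will be performed in a 1:1 ratio", after the baseline assessment.

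**The concern.** There are two separate problems.

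**Selection.** The arms are formed by randomisation, so the baseline tests address a null hypothesis that is true by design. A small p-value marks an unlucky draw; it does not show that the variable is related to change in binge eating. Under this rule an irrelevant variable at p = .04 enters the check, while a strong predictor of outcome at p = .08 does not.

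**Role.** Section 2.2.1 (Eligibility criteria) shows the underlying worry: if the arms differ in service use before treatment, change cannot be attributed to the intervention. That worry calls for covariate adjustment. A moderator of treatment × time asks whether the effect varies with the covariate, a question that the sample size in section 2.6 was not set for. It also makes the treatment × time coefficient conditional on one value of the moderator.

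At stake is how the main result is read. A check labelled as robustness can cast doubt on a sound finding, or appear to support it, for reasons unrelated to whether imbalance mattered.

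**Working it through.** **1. The plan's own figure.** Inputs from section 2.6: d = 0.50, "Power calculations using an intraclass correlation of .40", and "a power of .80, and an alpha level of .05 resulted in a required sample of *N* = 152". Two-sided alpha is assumed. Take a random-intercept growth model with times 0, 1, 2 and baseline SD 1.
- Slope difference: 0.50/2 = 0.25 per interval.
- Residual variance: 1 − 0.40 = 0.60. The centred times have sum of squares 2, so the variance of a person's slope is 0.60/2 = 0.30.
- n per arm = 2 × (1.960 + 0.842)² × 0.30 / 0.25² = 75.4, rounded up to 76. N = 152, power 0.803.

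The figure reproduces and does not depend on the rule in section 2.5.3.

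**2. How often the rule is triggered by chance.** For k independent tests at .05, P(at least one significant) = 1 − 0.95^k.

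| k (assumed) | P |
|---|---|
| 3 | 0.14 |
| 5 | 0.23 |
| 8 | 0.34 |
| 10 | 0.40 |
| 15 | 0.54 |

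Positively correlated variables would generally lower these values.

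**3. What the treatment × time coefficient becomes.** Write the person slope as a + b·T + c·x + m·x·T. If x is centred, b is the effect at the average x, with variance about 4 × 0.30/152 = 0.0079 (SE 0.089). If x is uncentred, b is the effect at x = 0 and its SE is multiplied by sqrt(1 + mean²/SD²). For an assumed age with mean 40 and SD 12, this is sqrt(1 + (40/12)²) = 3.5. A design-level z of 2.8 becomes 2.8/3.5 = 0.8.

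**4. Simulation check.** 12,000 trials per scenario, 76 per arm, complete data, least squares on person slopes. With complete balanced data this gives the same fixed-effect estimates as the random-intercept model. The covariate is age-like (mean 40, SD 12), with an assumed effect on the slope of 0.2 per SD. The true slope difference is 0.25.

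| Model | SD of estimate | Power |
|---|---|---|
| Unadjusted | 0.095 | 0.75 |
| Pre-named covariate with covariate × time | 0.089 | 0.80 |
| Moderator, centred | 0.089 | 0.80 |
| Moderator, uncentred, effect read at 0 | 0.317 | 0.125 |

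If the effect truly varies by 0.1 per SD, the uncentred coefficient targets 0.25 − 0.1 × 40/12 = −0.08, while the average effect is 0.25. The simulated mean was −0.08.

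**5. Does the moderator form adjust?** Take trials with no true effect in which this prognostic covariate happened to be significantly imbalanced (about 600 trials, so about ±2 points). Rejection rates were 8.1% unadjusted, 5.3% with covariate × time, 4.9% with the centred moderator and 3.7% with the uncentred one. With its lower-order terms, the moderator model contains covariate × time and does remove the imbalance.

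**The case against.** The strongest reply is that little depends on this step. It stands under additional analyses, and section 2.5 places moderator work in the last of its four steps. The primary test, its type I error and the sample size are all fixed elsewhere. All of that stands. A reader might infer that baseline tests decide the content of the effectiveness model; section 2.5.1 rules that out. Nor is the rule post hoc: the trigger and the three variable families are stated in advance, and only the resulting selection depends on the data.

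A reader might also infer that entering variables as moderators leaves imbalance uncorrected. Step 5 shows that this is not so in general.

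The loss of precision is conditional too. It needs an uncentred moderator and a reader who takes the coefficient at zero as the robustness result. The article states neither, and it refers to an R script in a supplement that is not shown, so its silence does not establish that centring is absent. For a categorical variable, zero is normally a reference group, and the problem takes a milder form.

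Finally, the higher trigger rates assume 10 to 15 independent tests; with 3 to 5 they are 14% to 23%. Section 2.5.3 also examines some covariates, such as outcome expectancies and attitudes, without a significance trigger.

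None of this defends the selection rule itself. The article states it as a positive rule, so it is not a detail left to an analysis plan.

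**Conclusion.** The point holds for the robustness check and only for it. The selection rule lets chance choose the model, passes over prognostic variables whose imbalance is not significant, and frames an adjustment question as one about effect heterogeneity. This part rests on the text and on randomisation alone.

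The numerical consequences rest on assumptions. The trigger rates depend on an unstated number of tests and on independence. The factor of 3.5 and the power of 0.125 depend on the assumed age distribution, no centring, and reading the coefficient at zero. They show what the wording permits, not what will happen. The documents do not support a conclusion that the confirmatory result is biased or that its error rate is inflated.

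Severity: minor to moderate.

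**What to change.** In section 2.5.3:
- Remove the baseline tests as a selection rule and describe baseline characteristics by arm.
- Specify one adjusted sensitivity model, run whatever the observed imbalance, with two or three pre-named baseline covariates, each centred and entered with covariate × time. Candidates already collected and named in section 2.5.2 are BMI, years since illness onset and global eating psychopathology (the EDE-Q total score). The last should be used only where it is not the outcome analysed, because its baseline value is then already the first repeated measure.
- State that the treatment × time coefficient from this model is the one compared with the main analysis.
- Keep moderator models as a separate exploratory analysis, with centred moderators and the three-way term as the quantity of interest.

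The cost is rewording two sentences and a small change to the analysis script. No new data are needed and the sample size is unchanged.

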#### Outcomes

2.4.3

Primary and secondary outcome measures will be assessed at baseline (study entrance), six weeks after baseline (mid-treatment), and 12 weeks after baseline (post-treatment). Moreover, to continuously evaluate core eating disorder symptoms, the occurrence of binge eating episodes and overeating will be monitored weekly, and traditional self-reports will be complemented by EMA using mobile technology to capture treatment outcomes and mechanisms in the natural environment and increase the ecological validity of our data. All measures will be collected using the computer software *SoSci Survey* (Leiner, 2021) and made available to participants at http://www.s2survey.net/. An overview of the clinical outcome measures based on the SPIRIT recommendations (Chan et al., 2013) is provided in Table 2.

**Table 2 t0010:** SPIRIT schedule of the randomized controlled trial.

	Study period				
	Enrollment	Allocation	Post-allocation		Close-out
		*Study entrance*	*Weekly*	*Mid-treatment*	*Post-treatment*
Timepoint	*−t*_*1*_	*t*_*1*_	*week*_*1*_*–week*_*12*_	*t*_*2*_	*t*_*3*_
Enrollment					
Eligibility screen	+				
Informed consent	+				
*Clinical interviews*					
Eating Disorder Examination Interview (EDE)	+				
Diagnostic Interview for Mental Disorders (DIPS-OA)	+				
*Allocation*		+			
Intervention					
12-week web-based intervention *Selfapy* for binge eating disorder			+	+	
12-week waiting time			+	+	
Assessments					
*Primary outcome*					
Number of Binge Eating Episodes (EDE-Q)		+		+	+
*Secondary confirmatory outcomes*					
Eating Disorder Examination Questionnaire (EDE-Q)		+		+	+
Weekly Binges Questionnaire(WBQ)		+	+	+	+
Clinical Impairment Assessment (CIA)		+		+	+
World Health Organization Well-Being Index (WHO-5)		+		+	+
*i*MTA Productivity Cost Questionnaire (*i*PCQ)		+		+	+
*Secondary exploratory outcomes*					
Patient Health Questionnaire Depression Scale (PHQ-9)		+		+	+
Generalized Anxiety Disorder Scale (GAD-7)		+		+	+
Rosenberg Self-Esteem Scale (RSES)		+		+	+
Difficulties in Emotion Regulation Scale (DERS)		+		+	+
Heidelberg Form for Emotion Regulation Strategies (HFERST)		+		+	+
Ecological Momentary Assessment (EMA)		+			+
*Other measures*					
Client Sociodemographic Service Receipt Inventory (CSSRI)		+		+	+
Negative Effects Questionnaire (NEQ)				+	+
Attitudes Towards Online Interventions (APOI)		+			+
Patients' Therapy Expectation and Evaluation Scale (PATHEV)		+		+	+

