
#### Other measures

2.4.7

•Attitudes towards online interventions: Two subscales of the *Attitudes Towards Psychological Online Interventions Scale* (APOI; Schröder et al., 2015) will be used to assess attitudes towards web-based interventions. The selected subscales consist of eight items rated on a 5-point scale and reliably measure perceived technologization threat (α = .64) and anonymity benefits of online interventions (α = .62; Schröder et al., 2015).•Patient outcome expectancies: Treatment motivation will be investigated using the *Patients' Therapy Expectation and Evaluation Scale* (PATHEV; Schulte, 2008). The PATHEV consists of 16 items answered on a 5-point scale and has been shown to reliably assess treatment motivation (α > .73; Schulte, 2005).•Negative intervention effects: The *Negative Effects Questionnaire* (NEQ; Rozental et al., 2019) will be utilized to capture possible side effects of the intervention. For each of the 32 items, participants answer whether an adverse effect occurred (yes/no), how it was (0 to 4) and if they attribute the negative effect to the web-based intervention or something else. The NEQ has an excellent internal consistency of Cronbach's α = .95 (NEQ; Rozental et al., 2019).•Use of other healthcare services: The *Client Sociodemographic Service Receipt Inventory – European Version* (CSSRI-EU; original: Chisholm et al., 2000; Roick et al., 2001) will be employed to assess the use of various other healthcare services (e.g., psychotherapy sessions, contact with psychiatrists). The CSSRI-EU has been validated as a reliable measure in clinical and non-clinical populations (Chisholm et al., 2000; Roick et al., 2001).•Patient adherence: The log files on the online platform (*Selfapy*) will be utilized to capture patient adherence within the intervention group. This includes the times and dates participants log into the intervention and the number of completed modules. Moreover, after six and twelve weeks (mid- and post-treatment assessment), participants in the intervention group will be asked to report how frequently they accessed the web-based intervention.

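### The stated harm analysis is a one-arm, self-attributed percentage, so it cannot show whether more patients worsen on the programme than on the waitlist

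*Protocol article*

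**What the plan says.** Section 2.5.3 (Additional analyses) names two patient safety indicators. The first is that "the percentage of participants in the intervention group who experienced adverse intervention effects caused by the web-based intervention will be quantified". The second is that "the amount of impairment due to these negative effects will be calculated". Both concern the intervention group's programme-related effects.

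Section 2.4.7 (Other measures) shows where the causal label comes from. For each NEQ item, participants say whether an effect occurred, rate it, and state "if they attribute the negative effect to the web-based intervention or something else".

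Table 2 in section 2.4.3 lists the "Negative Effects Questionnaire (NEQ") at mid-treatment and post-treatment. For the symptom measures the same section says: "Primary and secondary outcome measures will be assessed at baseline (study entrance), six weeks after baseline (mid-treatment), and 12 weeks after baseline (post-treatment"). Table 2 puts the EDE-Q binge count and the PHQ-9 at all three times, and neither row is limited to one arm.

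The between-arm model in section 2.5.1 is described thus: "we will examine if the change in symptom severity differs between the intervention and control group by adding the treatment × time interaction". The article states no other analysis of harm, adverse events or deterioration.

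**The concern.** The article fixes three features of the harm summary: one arm, only effects labelled as caused by the programme, and a label assigned by the patient. Together they set aside the randomised comparison, which section 3.1 presents as the trial's first strength.

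Some patients with binge eating disorder will get worse over 12 weeks for reasons unrelated to the programme, and some may blame the programme for it. Others may be harmed by the programme and put it down to something else; they drop out of the numerator. The percentage can therefore err in either direction, and without a waitlist figure its size cannot be judged. At stake is any statement in the trial report that the programme is safe, or no worse than waiting. The primary efficacy result is not at stake.

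**Working it through.** **Inputs.** Section 2.6 takes d = 0.50 ("we chose medium effect sizes of Cohen's *d* = 0.50 as a benchmark") and then uses "an intraclass correlation of .40 (Arend and Schäfer, 2019), a power of .80, and an alpha level of .05 resulted in a required sample of" 152. Section 2.3.1 allocates 1:1, so 76 per arm. Section 2.6 mentions 20% dropout in additional power analyses: 76 × 0.8 = 60.8, about 61 per arm. The documents give no worsening rate for either arm, so 5% to 20% is assumed below.

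**Step 1: reproduce the plan's own figure.** Take a random-intercept model with three equally spaced assessments, total SD 1 and ICC .40. The residual variance is 1 − .40 = .60, and the SD of the baseline-to-week-12 change is √(.60/.50) = 1.095. With two-sided alpha .05 (the article does not state sidedness) and power .80:

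n per arm = 2 × (1.960 + 0.842)² × 1.2 / 0.5² = 75.4, rounded up to 76, total 152.

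The stated N reproduces (power 0.803), with no inflation for dropout. This confirms 76 per arm as the basis for the precision figures. The point itself does not depend on it.

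**Step 2: can the one-arm figure be interpreted?** Suppose, for illustration, that 8 of 76 (10.5%) worsen on the programme. The risk difference, programme minus waitlist, has the Wald 95% CI d ± 1.96 × √[p₁(1−p₁)/76 + p₂(1−p₂)/76].

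| Waitlist worsening | Difference (points) | 95% CI |
|---|---|---|
| 8 of 76 | 0.0 | −9.8 to 9.8 |
| 15 of 76 | −9.2 | −20.5 to 2.1 |
| 3 of 76 | +6.6 | −1.6 to 14.8 |

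The same intervention-arm result fits no difference, a point estimate favouring the programme, or one against it. The planned summary cannot tell these apart.

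**Step 3: does the efficacy model fill the gap?** The treatment × time term estimates a difference in average change. If change were normal with the same SD in both arms, the mean would fix the proportion worsening. With SD 1.095, the proportion appearing more than 0.5 SD worse is P(Z > 0.5/1.095) = 32% at zero mean change and P(Z > 1.0/1.095) = 18% at a mean improvement of 0.5 SD. In that case the proportions only restate d = 0.5. The case that matters for safety is the other one, where most patients improve but a subgroup worsens. A favourable mean can hide that subgroup, and only a count by arm shows it.

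**Step 4: precision of a two-arm comparison.** With equal rates p in both arms, half-width = 1.96 × √[2p(1−p)/n]. The last column is the rate in the other arm that 76 per arm detects with 80% power.

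| Assumed rate | Half-width, 76 per arm | Half-width, 61 per arm | Detectable rate |
|---|---|---|---|
| 5% | 6.9 points | 7.7 points | about 20% |
| 10% | 9.5 | 10.6 | about 28% |
| 15% | 11.4 | 12.7 | about 35% |
| 20% | 12.7 | 14.2 | about 41% |

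Power for a 10-point excess with 76 per arm runs from 54% (5% base) down to 30% (20% base). If the rates were 32% and 18%, the half-width would be 1.96 × √[(.324 × .676 + .181 × .819)/76] = 13.6 points, and 15.2 points with 61 per arm.

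**The case against.** A reader might infer that the trial itself cannot show comparative harm. The documents do not support that: the symptom measures are scheduled without restriction to one arm, so the limit lies in the planned analysis and not in the design. The article also does not say these indicators are the only safety analysis, and it makes no comparative safety claim.

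A reader might also infer from Table 2 that the waitlist completes the NEQ. That is not established. None of the table's assessment rows separates the arms, section 2.4.7 describes the instrument as capturing side effects of the intervention, and attribution to the programme means little for people without access to it. A between-arm NEQ comparison may therefore be impossible.

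The 32% and 18% figures describe fluctuation in a symptom score. They say nothing about the size of the planned NEQ percentage, and a normal model is doubtful for 28-day binge counts.

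Patients who leave the study before week 6 give no NEQ data, but they give no follow-up EDE-Q or PHQ-9 either. The added comparison shares that gap and can only make it visible.

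Finally, a deterioration table is often left to the full analysis plan, and the R script in Supplement S2 is not shown. That would answer a complaint about something absent. It does not answer this one, because the article positively states the arm, the numerator and the causal filter. A descriptive summary of attributed effects is a legitimate use of the NEQ, but it cannot serve as a controlled safety estimate.

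**Conclusion.** The point holds against the harm analysis as stated in 2.5.3. That analysis has no reference rate and rests on lay attribution, and the planned models of mean change do not supply the missing comparison. A better analysis is available from data already scheduled.

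The gain is real but limited. A two-arm comparison would give an interval of roughly ±7 to ±14 points over the assumed 5% to 20% range, with or without 20% dropout, and wider if worsening is more common. It could reveal a large excess of deterioration but could not exclude a moderate one. These sizes rest on 1:1 allocation, equal rates in both arms and the Wald approximation; the worsening rates are assumptions. The change is worth making because it governs what may be said about safety. It changes no efficacy conclusion.

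**What to change.** In section 2.5.3:

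- Keep the NEQ attributed percentage and its impairment score, labelled as a descriptive summary of the intervention arm.
- Add a comparison of the arms as randomised on the proportion who deteriorate from baseline on the EDE-Q binge count and on the PHQ-9, at weeks 6 and 12. Fix the deterioration threshold in writing before group labels are released; the blinded data set described in section 2.3.1 makes this practicable.
- Report risk differences with 95% CIs, and beside them the number per arm without post-baseline data.
- Say that the comparison is an estimate and not a powered test.
- State whether the waitlist arm completes the NEQ. Only if it does, report NEQ occurrence by arm whatever the attributed cause.

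The cost is a few lines of text and one extra table, with no new assessments. The drawback is the wide interval, which should not be read as evidence of equal safety.
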